# Daylight photodynamic therapy versus cryosurgery for the treatment and prophylaxis of actinic keratoses of the face − protocol of a multicenter, prospective, randomized, controlled, two-armed study

**DOI:** 10.1186/s12895-017-0064-7

**Published:** 2017-10-25

**Keywords:** PDT, Study protocol, Cryosurgery, Methyl aminolevulinate, Daylight, AK, Skin aging, Prevention, Photorejuvenation

## Abstract

**Background:**

Photodynamic therapy with daylight (DL-PDT) is efficacious in treating actinic keratosis (AK), but the efficacy of field-directed, repetitive DL-PDT for the treatment and prophylaxis of AK in photodamaged facial skin has not yet been investigated.

**Methods/design:**

In this multicenter, prospective, randomized, controlled, two-armed, observer-blinded trial, patients with a minimum of 5 mild-to-moderate AK lesions on photodamaged facial skin are randomly allocated to two treatment groups: DL-PDT with methyl aminolevulinate (MAL) and cryosurgery. In the DL-PDT group (experimental group), 5 treatments of the entire face are conducted over the course of 18 months. After preparation of the lesion and within 30 min after MAL application, patients expose themselves to daylight for 2 h. In the control group, lesion-directed cryosurgery is conducted at the first visit and, in the case of uncleared or new AK lesions, also at visits 2 to 5. The efficacy of the treatment is evaluated at visits 2 to 6 by documenting all existing and new AK lesions in the face. Cosmetic results and improvement of photoaging parameters are evaluated by means of a modified Dover scale.

Primary outcome parameter is the cumulative number of AK lesions observed between visits 2 and 6.

Secondary outcome parameters are complete clearance of AK, new AK lesions since the previous visit, cosmetic results independently evaluated by both patient and physician, patient-reported pain (visual analogue scale), patient and physician satisfaction scores with cosmetic results, and patient-reported quality of life (Dermatology Life Quality Index). Safety parameters are also documented (adverse events and serious adverse events).

**Discussion:**

This clinical trial will assess the efficacy of repetitive DL-PDT in preventing AK and investigate possible rejuvenating effects of this treatment. (Trial registration: ClinicalTrials.gov Identifier: NCT02736760).

**Trial registration:**

ClinicalTrials.gov Identifier: NCT02736760. Study Code Daylight_01. EudraCT 2014–005121-13.

## Background

Actinic keratosis (AK) is one of the most frequently diagnosed skin diseases in dermatological practice. Clinical examination of the study participants of the Rotterdam cohort study aged >45 years showed a prevalence of up to 49% in men and 28% in women [1, 2]. Therefore, treatment of AK causes high costs for health insurances [3]. Consequent treatment of AK is necessary because of the possibility of malignant transformation. AK lesions are regarded as in situ squamous cell carcinomas [4] that progress to invasive squamous cell carcinomas in up to 20% of patients [5–7]. In 2015, ‘multiple actinic keratoses’ defined as more than 5 AK lesions per year or field cancerization of >4 cm^2^ have been acknowledged as a new occupational disease in Germany [8]. National and international guidelines recommend the treatment of AK upon diagnosis to prevent further progression into squamous cell carcinoma [9].

Besides several other treatment options, photodynamic therapy (PDT) with red light for illumination is characterized by high efficacy and good esthetic results, largely independent of patient adherence. Daylight-PDT (DL-PDT) is a new treatment approach that uses natural sunlight for illumination. DL-PDT is associated with less discomfort and pain compared to standard treatment protocols, and its efficacy in treating AK seems to be equal to that of conventional PDT with red light [10–12].

However, clinical trials investigating the efficacy of field-directed, repetitive DL-PDT for the prophylaxis of AK are lacking [11, 13, 14] as well as knowledge about the esthetic and rejuvenating effects of repetitive DL-PDT.

Therefore, the present study investigates the prophylactic effect of repetitive DL-PDT on the occurrence of AK as compared to lesion-directed cryosurgery. In addition, the rejuvenating effects of DL-PDT with regard to the clinical signs of photoaged skin are evaluated.

## Methods/design

### Study design

This study was designed as a multicenter, prospective, randomized, controlled, two-armed study that compares two different treatments. MAL application followed by illumination with daylight (DL-PDT) represents the experimental treatment, and cryosurgery as a standard lesion-directed therapy of AK is investigated as a reference therapy. Patients are randomly allocated to one of the two treatment methods.

The study was approved by the Institutional Review Board and the Ethics Committee of the University of Regensburg (Approval number: 15–112-0068) as well as by the German Federal Institute for Drugs and Medical Devices (Approval number: 61–3910-4,040,415). The study was registered at EU Clinical Trials Register (EudraCT Number: 2014–005121-13) on November the 17th 2014 and at clinicaltrials.gov (ClinicalTrials.gov Identifier: NCT02736760) in March 2016. The clinical trial was not registered retrospectively. The SPIRIT guidelines were followed in this study protocol.

Written informed consent will be obtained from each patient before enrolment. This is an ongoing clinical trial.

### Inclusion and exclusion criteria

The main inclusion criteria are clinical diagnosis of actinic keratosis (AK), a minimum of 5 non-hyperkeratotic, non-pigmented AK lesions in the face (Olsen grading I or II), Glogau Photodamage Classification Type II (moderate) to IV (severe), Fitzpatrick skin type I to IV, age ≥ 40 years, a negative pregnancy test in women of child-bearing age, and written informed consent (Fig. 1).

**Fig. 1 Fig1:**
[figure not shown]
Potential study patient. Face of a potential study participant with Glogau Photodamage Classification Type III (advanced). Multiple visible AK, sallow skin discoloration with teleangiectasias and wrinkles

The main exclusion criteria are known intolerance or allergy to MAL or to any other ingredient of Metvix® 160 mg/g cream or Actinica® lotion (both Galderma Laboratorium GmbH, Düsseldorf, Germany), photosensitivity, diagnosis of porphyria, hyperkeratotic or pigmented AK in the face, malignant skin tumors in the face or on the scalp, clinically relevant suppression of the immune system, pregnancy or lactation, medical history of PDT in the face during 6 months preceding study treatment, rejuvenating treatment of the face 3 months preceding study treatment or planned esthetic treatments in the face in the next 24 months, other topical treatments of AK in the face during 4 weeks preceding study treatment or systemic treatment with retinoids, and suspected lack of compliance (e.g. dementia).

### Study treatment

At every visit, the location of each AK lesion is documented within a chart and additionally marked on plastic sheets. The plastic sheets are marked with reference points of the face of each study participant, ensuring that the lesions will be found again at the next visit. Photo-documentation is carried out in a standardized manner at each visit.

Photodamage variables to be evaluated are fine lines, mottled pigmentation, skin color, tactile roughness, sallowness, teleangiectasias, deep wrinkles, facial erythema, sebaceous gland hyperplasia, and the global score for photoaging. Each photodamage variable is recorded on a 5-point scale (0–4, higher points indicating higher damage, modified after a scale from Dover et al. and Zane et al.) (Table 1) [15, 16].

**Table 1 Tab1:** Photodamage Score

Score	0	1	2	3	4
Global score for photoaging	facial skin smooth to the touch, no significant fine lines, uneven pigmentation, deep wrinkles, erythema, teleangiectasias, sebaceous gland hyperplasia on the cheeks, forehead, or in the perioral area	one area (cheeks, forehead, or perioral area) of significant roughness, deep wrinkles, erythema, teleangiectasias, sebaceous gland hyperplasia, dyspigmentation or fine lines	two areas of significant roughness, deep wrinkles, erythema, teleangiectasias, sebaceous gland hyperplasia, dyspigmentation or fine lines or one area of significant roughness, deep wrinkles, erythema, teleangiectasias, sebaceous gland hyperplasia, dyspigmentation and fine lines	three areas of significant roughness, deep wrinkles, erythema, teleangiectasias, sebaceous gland hyperplasia, dyspigmentation or fine lines or one area of significant roughness, deep wrinkles, erythema, teleangiectasias, sebaceous gland hyperplasia, dyspigmentation and fine lines	facial skin with photodamage higher than grade 3
Fine lines	none	very few, widely disseminated lines	some discreet lines	a moderate number of lines, in close proximity	many lines, in close proximity
Mottled pigmentation	evenly pigmented skin	minor hypo-pigmentation or hyper-pigmentation	small areas of very light hypo-pigmentation or hyper-pigmentation or moderately sized areas of light hypo-pigmentation or hyper-pigmentation	moderate hypo-pigmentation or hyper-pigmentation or small areas of pronounced hypo- pigmentation or hyper-pigmentation	major hypo- pigmentation or hyper-pigmentation
Skin color	pale pink	pale	yellowish, greyish	pale, slightly yellowish-greyish	pale, distinctly yellowish-greyish
Tactile roughness	soft skin	soft, some rough areas	minor roughness	moderate roughness	major roughness
Teleangiectasias	none	rare, widely disseminated	some discreet teleangiectasias	a moderate number of teleangiectasias, in close proximity	many teleangiectasias, in close proximity
Deep wrinkles	none	superficial wrinkles in one area	superficial wrinkles in more than one area or moderately deep wrinkles in one area	moderately deep wrinkles in more than one area or deep wrinkles in one area	deep wrinkles in more than one area
Facial erythema	none	small areas with slight erythema	small areas with moderate erythema or moderately sized areas with slight erythema	moderately sized areas with erythema	large areas with erythema
Sebaceous gland hyperplasia	none	some in one area	some in several areas or several in one area	a moderate number in several areas or many in close proximity in one area	many in close proximity in more than one area

Photodamage variables to be evaluated are fine lines, mottled pigmentation, tactile roughness, sallowness, teleangiectasias, and global score for photoaging. Each photodamage variable is recorded on a 5-point scale (0–4, higher points indicating higher damage, modified after Dover 2005 und Zane 2007)

**Table 2 Tab2:** Study flow chart

Time	- 4 weeks – 0 d+	d 0+	3 months after V1^#^	3 months after V2^#^	6 months after V3^#^	6 months after V4^#^	6 months after V5^#^
Visit	Screening	1	2	3	4	5	6
Study treatment Test-group: Fullface-Daylight-PDT		1.PDT	2.PDT	3.PDT	4.PDT	5.PDT	
Study treatment Control-group: cryosurgery		Cryo	Cryo°	Cryo°	Cryo°	Cryo°	
Documentation of AK lesions in the face		X	X	X	X	X	X
Randomization	X						
Obtaining Informed Consent	X						
Check of Inclusion/ Exclusion Criteria	X	X	X	X	X	X	X
Medical history	X						
Photodocumentation		X	X	X	X	X	X
Assessment of photoaging parameters		X	X	X	X	X	X
Documentation of newly occurred malignant skin tumors in the face		X	X	X	X	X	X
Documentation of AEs and SAEs		X	X	X	X	X	X
Pain score (VAS) during treatment		X	X	X	X	X	
Skin-related quality of Life (DLQI)	X						X
Patient satisfaction with cosmetic results			X	X	X	X	X
Investigator satisfaction with cosmetic results			X	X	X	X	X
Local skin reactions		X	X	X	X	X	
Pregnancy test	X	X	X	X	X	X	

+: Screening and Visit 1 may take place on the same day

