### Outcome assessment

The primary outcome parameter is the cumulative number of AK lesions observed between visits 2 and 6.

Secondary outcome parameters are complete clearance of AK on patient and lesion basis, new AK lesions since the last visit, cosmetic results as evaluated on assessment scales, patient-reported pain (visual analogue scale, VAS), local reactions, patient satisfaction score with cosmetic results, physician satisfaction score with cosmetic results, and patient-reported quality of life (Dermatology Life Quality Index, DLQI).

In addition, safety parameters are documented (adverse events and serious adverse events, AE and SAE).

Complete clearance is documented if a lesion is no longer visible and also imperceptible to the touch [17]. Photodamage variables to be evaluated are fine lines, mottled pigmentation, skin color, tactile roughness, sallowness, teleangiectasias, deep wrinkles, facial erythema, sebaceous gland hyperplasia, and global score for photoaging. Each photodamage variable is recorded on a 5-point scale (0–4, higher points indicating higher damage, modified after Dover and Zane) [15, 16].

Patient and physician satisfaction with esthetic outcome is assessed at visit 2 to 6. Patients and physicians can choose from very satisfied, satisfied, moderately satisfied, and not satisfied.

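### Table 1 gives grades 2 and 3 of the global photoaging score the same second criterion, and the lists of photodamage variables in text, table and footnote disagree

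*Protocol article*

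**What the plan says.** The photodamage scale is printed in the protocol article, Study treatment, Table 1. Every variable is to be graded 0 to 4, with a higher grade meaning more damage.

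- **Global score, grade 2** begins: "two areas of significant roughness, deep wrinkles, erythema, teleangiectasias, sebaceous gland hyperplasia, dyspigmentation or fine lines or one area of significant roughness".
- **Global score, grade 3** begins: "three areas of significant roughness, deep wrinkles, erythema, teleangiectasias, sebaceous gland hyperplasia, dyspigmentation or fine lines or one area of significant roughness".
- Both cells end with the same alternative: "one area of significant roughness, deep wrinkles, erythema, teleangiectasias, sebaceous gland hyperplasia, dyspigmentation and fine lines".
- **Grade 4** reads in full: "facial skin with photodamage higher than grade 3".

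The body text of Study treatment lists "Photodamage variables to be evaluated are fine lines, mottled pigmentation, skin color, tactile roughness, sallowness, teleangiectasias, deep wrinkles, facial erythema, sebaceous gland hyperplasia" and then the global score. Outcome assessment gives the same list: "fine lines, mottled pigmentation, skin color, tactile roughness, sallowness, teleangiectasias, deep wrinkles, facial erythema, sebaceous gland hyperplasia, and global score for photoaging". The footnote to Table 1 is shorter: "Photodamage variables to be evaluated are fine lines, mottled pigmentation, tactile roughness, sallowness, teleangiectasias, and global score for photoaging".

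In the skin color row, grade 2 is yellowish and greyish without any qualifier, while grade 3 is "pale, slightly yellowish-greyish".

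The Discussion names the rejuvenating effect as a secondary endpoint. Statistical analysis treats all secondary endpoints as exploratory and descriptive. Table 2 schedules the photoaging assessment at visits 1 to 6.

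**The concern.** An ordinal scale works only if each face belongs to one grade and the grades rise in order. Here the boundary between global grades 2 and 3 is undefined for some faces. Different raters, different centres, or one rater at different visits could record 2 or 3 for the same skin. The trial is multicenter, scores the scale at six visits and enrols patients with moderate to severe photodamage (Glogau II to IV), so the upper part of the scale is likely to be used.

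The conflicting lists raise a separate question: how many items make up the cosmetic outcome, and whether skin color and sallowness are one item or two. A descriptive analysis does not remove either difficulty, because a table of grades can be read only if the grades are defined.

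**Working it through.** No sample size, power or alpha enters this point, and the plan gives no figure to reproduce. The check sets the printed texts side by side.

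**Step 1: the global score row.** I read the list joined by *or* as any one sign, and the list joined by *and* as all signs together.

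| Grade | First alternative | Second alternative |
|---|---|---|
| 1 | one area, any sign | none |
| 2 | two areas, any sign | one area, all signs |
| 3 | three areas, any sign | one area, all signs |
| 4 | defined only relative to grade 3 | none |

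The first alternatives of grades 2 and 3 differ. The second alternatives are identical when compared as text.

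**Step 2: which faces are affected.** Let *k* be the number of affected areas out of three (cheeks, forehead, perioral).

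- No area with all signs: *k* = 1, 2, 3 gives grade 1, 2, 3. There is no conflict.
- One area with all signs and *k* = 3: the three-area criterion supports grade 3 in its own right.
- One area with all signs and *k* = 1 or 2: the second alternative is met under both grade 2 and grade 3. Nothing printed decides between them.

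Size for each affected face: 3 − 2 = 1 point. The range is 4 − 0 = 4, so the ambiguity is 1/4 = 25% of the scale. The frequency of such faces is not given.

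Grade 4 depends on where grade 3 ends. No rule says, for example, whether all signs in two areas already exceeds grade 3.

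**Step 3: the variable lists.**

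- Text (Study treatment and Outcome assessment): 10 variables, with skin color and sallowness separate.
- Table 1: 9 rows. The listed variable without a row is sallowness (10 − 9 = 1).
- Footnote: 6 variables. It omits skin color, deep wrinkles, facial erythema and sebaceous gland hyperplasia (10 − 6 = 4), but includes sallowness, which has no row.

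**Step 4: the skin color row.** The sequence is pale pink, pale, an unqualified yellowish and greyish tone (grade 2), the same tone qualified as slight (grade 3), and the same tone qualified as distinct (grade 4). By its wording, grade 3 is not clearly worse than grade 2.

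**Step 5: what is left.** Of the 10 listed variables, 3 are affected (global score, sallowness, skin color). The other 10 − 3 = 7 each have five separate anchors: fine lines, mottled pigmentation, tactile roughness, teleangiectasias, deep wrinkles, facial erythema and sebaceous gland hyperplasia.

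**The case against.** The strongest reply has four parts.

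1. **The overlap may be rare.** It needs one area with all seven signs present together, and fewer than three affected areas. This stands: the documents give no frequency. A rater might also simply take the highest grade met, but then the second alternative under grade 2 would never decide a grade, and no such rule is printed.
2. **Sallowness is probably the skin color row under another label.** The row's anchors describe a yellowish-greyish tone, and the footnote names sallowness while leaving out skin color. This is the likelier explanation. Even so, the text twice lists the two as separate items, so the plan has to settle it.
3. **The centres' scoring sheet is not shown.** The article proves that its printed table contradicts itself, not that raters used that wording. This stands and decides the first step of the fix.
4. **The endpoint is secondary and exploratory.** This stands and limits the weight of the point.

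A reader might infer three stronger things that the documents do not support:

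- *The whole rejuvenation endpoint cannot be scored.* Seven of the ten listed variables have usable anchors.
- *One variable certainly has no anchors.* That is so only if sallowness is truly distinct from skin color.
- *The mean global score will drift, or one arm will be favoured.* The net shift in the mean is the share of faces moved up minus the share moved down, times one point. Chance disagreement goes both ways and largely cancels, leaving noise. A drift would need an assumed frequency, which has no source here, and movement in one direction. The trial is described as observer-blinded, and nothing in the table's wording favours an arm.

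**Conclusion.** The point holds as an internal contradiction in a printed scoring rule. For faces with one area showing all signs and fewer than three affected areas, the global score is ambiguous by one point on the 0–4 scale, and the grade 4 boundary inherits this. The variable lists (10, 9 and 6) need reconciling, and skin color grades 2 and 3 are not clearly ordered.

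The conclusion rests on Table 1 as printed and on the ordinary reading of *or* and *and* in its cells. How many patients are affected is unknown, and so is whether centres used this wording. The global score, sallowness and skin color are affected. The primary endpoint and the sample size are not. It should be corrected because the rejuvenating effect is a named aim of the trial and the correction is cheap, but it does not threaten the trial's main conclusion.

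**What to change.** 1. Compare the scoring sheet used at the centres with Table 1. If the sheet is free of these conflicts, a published correction of the table, footnote and variable list is enough.
2. Give global grades 2 and 3 mutually exclusive criteria, or state a tie-break, and define grade 4 so that it no longer depends on an ambiguous grade 3.
3. Put the skin color anchors in increasing order.
4. State that skin color is the sallowness item and remove the duplicate, or add a sallowness row.
5. Use one variable list in the text, the table and the footnote.

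If the centres did use the printed wording, apply one common tie-break to all visits, including baseline. Recorded item scores and stored photographs can serve only as a check. A face scored 0 on any of the seven sign items cannot have met the duplicated clause, so item scores can exclude candidates. They cannot confirm them, because the items are not all recorded by area. Roughness is judged by touch and cannot be scored from photographs.

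The cost is a corrected sheet and table, plus a check of some recorded global grades so that baseline and follow-up stay on one scale.

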# +/− 4 weeks

Cryo: Cryosurgery

° cryosurgery in the case of uncleared or newly developed AK lesions

Patient and investigator satisfaction with the cosmetic outcome is evaluated from visit 2 onwards according to the following scale: very satisfied, moderately satisfied, slightly satisfied and not satisfied.

Pain during treatment is assessed by means of a visual 11-point scale (VAS-scale, 0, none, to 10, insufferable pain). The patients mark their level of pain on the VAS. The investigator rates and documents erythema and edema after illumination with daylight or cryotherapy by means of a 5-point scale: 0 (no), 1 (mild), 2 (moderate), 3 (marked), and 4 (severe). From the second visit onwards, patients are asked if they have experienced any side effects or any adverse events. (Table 2)

#### MAL application followed by illumination with daylight

Each patient randomized to the PDT arm of this trial receives 5 treatments with daylight PDT. For each PDT session, an organic sunscreen (Actinica® lotion, LSF 50+, Galderma Laboratorium, Düsseldorf, Germany) without any mineral filters is applied onto the entire face and other parts of the body that will be exposed to daylight. After an absorption time of at least 15 min, the surface of the AK lesions is gently prepared with a curette or a scalpel to remove scales and crusts and to roughen the lesions’ surface. Then, a thin layer of MAL cream (Metvix®, Galderma Laboratorium, Düsseldorf, Germany) is uniformly applied onto the entire face including the hairless forehead, but sparing the eyelids, lips, and ears. Covering the entire face with a thin layer using a spatula approximately requires 1 tube (2 g) of MAL cream. No occlusive dressing is conducted. Within 30 min after MAL application, patients expose themselves to daylight for 2 h. After daylight exposure, patients return to the clinic or practice and are instructed in washing off the MAL cream with clear water. This treatment regimen is provided at visit 1 and repeated after 3 months, 6 months, 12 months, and 18 months (visits 1 to 5). DL-PDT can only be carried out from March until October, in non-rainy weather, and an outdoor temperature of at least 10 °C.

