#### Cryosurgery

In the control-group, one single freeze–thaw cryosurgery is conducted at visit 1, using an open spraying procedure with liquid nitrogen for each AK lesion. After formation of an ice ball, freeze time starts that should be between 5 and 10 s per lesion. At visits 2 to 6, the efficacy of the treatment is evaluated by the investigator. Cryosurgery will also be conducted at visits 2 to 5 in the case of non-cleared or newly developed AK lesions.

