#### Statistical analysis

The cumulative number of AK lesions (sum of all AK lesions from visit 2 to visit 6) is defined as the primary endpoint. A point estimate is presented as mean and standard deviation accompanied by the corresponding 95% confidence interval. Furthermore, the primary endpoint is compared between the MAL/daylight-PDT and the cryosurgery group by means of an analysis of covariance (ANCOVA) with treatment (MAL/daylight-PDT and cryosurgery) as fixed factor and initial AK at baseline and center as covariates. The results are presented in terms of least-squares means and associated 95% confidence intervals. All efficacy analyses are carried out on the intention-to-treat (ITT) population and will be two-sided at the significance level of 0.05.

All secondary endpoints are analyzed in a purely exploratory manner and are summarized by means of descriptive statistics. Thus, *p*-values and corresponding confidence intervals are only descriptive in nature. Safety variables are analyzed descriptively. Adverse events are presented in frequency tables. In addition, adverse events are tabulated by severity and relationship to study treatment.

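### Five daylight-PDT sessions fit the March–October season only for early-season starts; because cryosurgery visits have no season rule, the primary lesion counts can be taken at different times in the two arms

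*Protocol article*

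**What the plan says.** In the protocol article, the section on MAL application followed by daylight sets the number of sessions: "Each patient randomized to the PDT arm of this trial receives 5 treatments with daylight PDT". The regimen starts at visit 1 and is "repeated after 3 months, 6 months, 12 months, and 18 months (visits 1 to 5"). The same section limits when a session may take place: "DL-PDT can only be carried out from March until October, in non-rainy weather", and it must be 10 °C or warmer outdoors.

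Table 2 (study flow chart) times each visit from the one before; visit 3, for instance, is "3 months after V2". Its footnote allows 4 weeks either side. One time row serves both arms. The row "Documentation of AK lesions in the face" is ticked at visits 1 to 6, so at visits 2 to 5 the count and the daylight-PDT session share a visit. Table 2 places randomisation at screening, up to 4 weeks before visit 1.

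For the control arm, the Cryosurgery section says: "Cryosurgery will also be conducted at visits 2 to 5 in the case of non-cleared or newly developed AK lesions". It states no season or weather condition.

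Under Statistical analysis, the primary endpoint is the "sum of all AK lesions from visit 2 to visit 6". It is compared by ANCOVA with baseline AK count and center as covariates.

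**The concern.** A session interval of 3 or 6 months and a closed season of 4 months (November to February) are compatible only for some starting dates. For other dates the daylight-PDT visit has to move, or the session falls outside the rules. The season rule binds one arm only, so a cryosurgery patient who starts on the same day can keep the nominal date.

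This matters because the primary endpoint is built from counts taken at those visits. The number of lesions seen at a visit plausibly depends on the time since the last treatment and on how long new lesions have had to appear. If visit 3 comes around month 4.5 in one arm and month 6 in the other, the two sums do not cover the same follow-up. Visits 4 to 6 are timed from the preceding visit and can inherit the shift. Randomisation does not balance a shift that is caused by the treatment rule itself, and neither ANCOVA covariate describes visit timing.

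**Working it through.** **Inputs.** Sessions at visits 1–5 and the season rule come from the daylight-PDT section. Intervals of 3, 3, 6 and 6 months from the previous visit, with a window of ±28 days, come from Table 2. The two sources agree on nominal times: 3; 3 + 3 = 6; 6 + 6 = 12; 12 + 6 = 18 months.

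**Assumptions.** The season runs from 1 March to 31 October inclusive, which is 245 days. Months are calendar months. Rain and the 10 °C limit are not modelled; they can only narrow the fit.

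**Step 1: nominal dates.** Visit 3 is visit 1 + 6 months and must fall by 31 October. A 30 April start gives 30 July, 30 October, 30 April and 30 October, so all sessions fit. A 1 May start puts visit 3 on 1 November, which does not. Feasible starts are 1 March to 30 April: 61/245 = 25%.

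**Step 2: Table 2's chained window.** The earliest visit 3 uses both intervals at 3 months minus 28 days.
- 25 June start: 25 September − 28 days = 28 August (day 64); 28 November − 28 days = 31 October (day 128). It fits, with a single allowed day for each of visits 2 and 3.
- 26 June start: the same steps give 1 November, one day too late.
- Waiting until spring also fails. With visit 2 on 31 October, the latest visit 3 is 31 January + 28 days = 28 February, before the season opens.

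A day-by-day search over visit-1 dates confirms 1 March to 25 June, 117/245 = 48%, for starts in each year from 2015 to 2018.

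**Step 3: what compliance requires inside that range (2017 dates).**

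| Visit 1 | Nominal visit 3 | Daylight-PDT visit 3 allowed | Earlier than nominal by at least |
|---|---|---|---|
| 1 May | day 184 | day 128–183 | 1 day |
| 15 June | day 183 | day 128–138 | 183 − 138 = 45 days |
| 25 June | day 183 | day 128 only | 183 − 128 = 55 days |

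Without the season rule, as for cryosurgery, visit 3 may fall on day 128–240 for each of these starts. The upper end needs two consecutive latest visits, so the fair comparison is with the nominal day.

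**Step 4: how badly later starts miss.** The smallest window per visit that would make each start feasible (2017) is:
- 26 June to 31 August: 29–30 days, so 1–2 days beyond the stated 28.
- September: 31–60 days. October: 29–59 days. Of these 61 start days, 49 need more than 35 days and 35 need more than 42.

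The 28-day boundary is therefore sharp. A 29-day window raises the feasible days from 117 to 179 of 245 (73%) for 2016–2018 starts, though only to 119 for 2015 starts because of the leap day. A 30-day window gives 186 (185 for 2015).

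**Step 5: sensitivity to reading.**
- Windows counted from visit 1 rather than the previous visit: 1 March–28 May plus about 1–28 August (89 + 28 = 117 days in 2017).
- Months taken as 13 weeks or 30.44 days: last feasible start 27 June. As 30 days: 29 June.
- Season ending 30 September: last feasible start 25 May, or 31 March at nominal dates.

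**The case against.** The strongest reply is that the document can be followed as written. A March or April start satisfies every rule at nominal dates, and the article gives no enrolment calendar. Seasonal recruitment limits and the handling of out-of-season sessions are matters an article may leave to the full protocol. That stands: their absence is not counted as a fault, and all shares above are of calendar days, not of patients.

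Second, Table 2 gives both arms the same visit times and window, and nothing says that cryosurgery visits will be scheduled differently. That is correct, and it is why the point is that timing can differ, not that it does. But the one rule that moves visits is attached to daylight-PDT alone, and a shared window does not make the arms move together.

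Third, the 25 June limit depends on chaining and on the exact 28 days. This also stands. Counting from visit 1 would admit most August starts and exclude 29 May to 25 June, and one extra day would rescue most July–August starts. Under either anchoring, though, starts from 1 to 28 May need an early visit 3, and most September–October starts miss by a wide margin under the chained window.

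A reader might infer that the schedule is unworkable for half of the patients, or that the primary comparison is biased toward one treatment. The document supports neither. It does not show when patients start, and it gives nothing from which the effect of a shifted count on the sum could be calculated.

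**Conclusion.** The point holds as a design weakness that should be fixed. The stated session times and season rule agree at nominal dates only for visit 1 between 1 March and 30 April, and under Table 2's chained window only up to 25 June. From 1 May onward, full compliance requires an early visit 3 in the daylight-PDT arm, by at least 45 days for a mid-June start, while a cryosurgery patient may attend at the nominal date. The counts that make up the primary endpoint can therefore be taken at different times by arm without any protocol deviation.

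This rests on reading October as wholly inside the season and on calendar months; other conventions move the boundary dates but do not remove the conflict. Size and direction of any bias are unknown. If all patients start in March or April, or if the full protocol already puts both arms on one calendar, the practical effect would be small.

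**What to change.** Before randomisation, use the planned visit-1 date to fix one visit calendar for the patient that is compatible with the daylight-PDT season. Apply that calendar, with the same windows, whichever arm is allocated. Any seasonal shift of visits 2 to 6 then applies equally to cryosurgery patients. For a May or June start, for example, visit 3 would be due by 31 October in both arms. Setting the date before allocation also prevents the visit-1 date from depending on the arm. As the trial is ongoing, patients already enrolled can follow the common calendar for their remaining visits.

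Preferably plan visit 1 in March or April, so that nominal dates hold, and accept May–June starts only on the shifted common calendar. The 25 June date should not be used as a working limit: it leaves one permitted day for each of visits 2 and 3 before rain or cold is considered. Nor should the count be kept on time while a weather-delayed session is moved to a later day. That would shorten the time from treatment to the next count in the daylight-PDT arm only, creating a new difference between arms.

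The cost is amendment wording and less scheduling freedom for cryosurgery patients. If starts are restricted to March–April, there are 61 start days a year instead of 245, which may lengthen enrolment. The common calendar by itself needs no additional patients.
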